### Study Sample and Recruitment

A combination of convenience and snowball sampling will be used for the purposes of this study. To be eligible, participants must be aged ≥60 years, living in a community setting in Canada, and able to communicate in English and provide consent on their own behalf. The participants must have access to a computing device (computer or tablet) and a reliable internet connection at their place of residence to complete the web-based assessments and tasks. Participants in both groups must be able to safely participate in light to moderate unsupervised activity without requiring a physician’s approval as assessed using the Get Active Questionnaire (GAQ) [55,56]. Exclusion criteria include (1) diagnosis of moderate or severe dementia or a score <18 on the Montreal Cognitive Assessment (MoCA; version 8.1-Telemed) [57,58]; (2) self-reported severe motion sickness or commonly experienced motion sickness or nausea when driving or sitting in a car, train, or bus; (3) self-reported hearing impairment that may interfere with the participant’s ability to hear and understand the auditory cues in the cognitive and perceptual tasks; (4) uncorrected visual impairment (eg, cataracts, glaucoma, or macular degeneration) that may interfere with the participant’s ability to see and interact with the game and perform the cognitive and perceptual tasks; (5) ear infection in the previous 12 months or a diagnosis of a disease of the middle ear, such as Meniere disease; and (6) any preexisting conditions that would prevent them from engaging in exercise, including having a cardiac pacemaker. The same inclusion and exclusion criteria will be used for both the experimental and control groups to ensure internal validity.

### VR Intervention

#### Software

For the VR exergame intervention in this study, the participants will play a custom-made VR exergame, *Seas The Day*, on an Oculus Quest 2 (Facebook Reality Labs) headset [59,60]. *Seas The Day* was designed using an extensive user-centered and participatory design process with various stakeholders, including older adults, exercise professionals, game designers, engineers in the field of human factors and assistive technologies, and a local VR studio [61]. The VR exergame simulates a remote tropical island with several different activities that are intended to encourage upper-body physical activity. The game is designed to be played seated so that fall risk is minimized. Each exergaming session lasts 15 to 20 minutes.

*Seas The Day* (Figure 1) includes 3 virtual locations with three different activities: (1) a tai chi warm-up, (2) a rowing conditioning exercise, and (3) a fishing cooldown. Recorded audio clips guide the participants on game activities alongside visuo-tactile cues to facilitate interaction. No buttons are needed to interact with the virtual elements. Players are automatically transported from one game stage to the next to prevent interaction errors.

**Figure 1 figure1:**
[figure not shown]
Screenshots of the *Seas The Day* exergame showing the tropical virtual environment and some of the activities.

#### Hardware

*Seas The Day* is designed to be played in stand-alone VR headsets. In this study, an Oculus Quest 2 will be used because of its widespread availability, relatively low weight (compared with other VR headsets), and performance when running the designed game. Two main hardware modifications will be made to the headset: (1) the conventional foam cover will be replaced with a silicon cover to facilitate cleaning and sanitization of the headset and (2) the conventional strap will be replaced with a more comfortable strap (ie, Elite Strap) [62], which allows for a more simplified way to adjust the headset (Figure 2 and Multimedia Appendix 1).

**Figure 2 figure2:**
[figure not shown]
Participants playing the *Seas The Day* exergame using Oculus Quest 2 (Facebook Reality Labs).

### Procedure

The participants will be asked to play *Seas The Day* 3 times a week for 6 weeks. *Seas The Day* will be the only game that the participants will have access to in the provided VR headset. The participants will be encouraged to maintain consistency in engaging with the VR exergame by playing in the mornings and preferably on the same days every week. They will be notified that each exergame session will take approximately 15 to 20 minutes and encouraged to achieve a light to moderate intensity when playing the game. Setup and ongoing participation in the intervention will be supported in a number of ways. First, the participants will be provided with step-by-step software and hardware manuals (Multimedia Appendix 2). Second, each participant will meet with the study staff or trainees for a remote introductory session via a videoconference platform. The team member will show the participants how to use the system while sharing their screen so that the participants can see and become familiar with the visual information and the overall interaction with the system. The team member will also demonstrate how to calibrate the system and play the game, stage by stage, and answer any questions as they arise. The participants will then be encouraged to interact with the system and try playing the exergame in the presence of the team member and speaking aloud about what they are seeing and experiencing so they can be guided if facing any difficulties. Finally, the participants will be able to contact the study staff and trainees to troubleshoot the system via email, phone, SMS text message, or video calls at any time as most appropriate for the situation and the participant’s comfort. To facilitate troubleshooting video calls, the participants will be offered screen-sharing options to facilitate the explanation as well as a view from the frontal camera of the computer to see how the team member is located and moving in the physical space.

### Ethics Approval

This study has been reviewed and received ethics clearance through the University of Waterloo Research Ethics Committee (experimental group 42908, control group 43379).

### Data Collection and Assessments

#### Screening

The participants will complete a verbal informed consent agreement before taking part in the study and will be screened (via email or telephone) for eligibility using (1) a custom-made screening questionnaire and (2) the GAQ. The custom-made screening questionnaire is developed by the research team and includes questions on the study’s inclusion and exclusion criteria. The GAQ, developed by the Canadian Society for Exercise Physiology [56], is a prescreening measure for physical activity to ensure the participants’ safety when partaking in at-home exercise. The GAQ includes sections on preparing to become more physically active, assessing current physical activity, and general advice for becoming more active. A record of ineligible cases and those who did not provide consent to participate in the study will be kept in the screening log to inform the recruitment process. No further information will be collected from these cases.

#### Demographics

Background and demographic data will be obtained through (1) a demographic questionnaire, (2) the remote MoCA (version 8.1-Telemed) [58], and (3) the short version of the Geriatric Depression Scale-15 (GDS-15) [63]. The demographic questionnaire is developed by the research team and collects basic information of the participants (eg, age, sex, gender, and education), their health (eg, perceived physical and mental well-being, history of falls, and hearing and vision impairments), and previous experiences with gaming and motion sickness. The MoCA is a validated screening tool for cognitive impairment with high sensitivity and specificity for detecting mild cognitive impairment and dementia [57]. The MoCA will not be used for diagnostic purposes but will be used by the researchers to gain insight regarding the sample’s baseline cognition (a MoCA score of <13 suggests severe cognitive impairment; this study will use a cutoff score of ≥18 for study inclusion). The remote audiovisual administration of the MoCA will be conducted by a trained researcher. The GDS-15 is a widely used depression assessment tool that is specifically designed for older adults. Similar to the MoCA, the purpose of using the GDS-15 is to gain insight into the sample’s baseline depressive symptoms (if any). The GDS-15 consists of 15 questions about how the participant has felt over the previous week.

#### Outcomes and Measures

##### Overview

All participants will complete assessments at baseline and after the intervention (follow-up). Upon completion of the study (in a period of 8 weeks), semistructured focus groups or interviews will be conducted (with distinct questions for the control vs the experimental groups), and informal notes and reports will also be obtained from both the experimental and control groups. All participants will complete the exercise self-efficacy questionnaire; further acute changes in executive function, multisensory integration, and mood before and after gameplay or reading will also be assessed. In addition, the experimental group will complete the RPE [64] and perceived enjoyment scales upon completion of each exergaming session. All questionnaires except for RPE and perceived enjoyment for the experimental group will be completed on the web using Qualtrics survey software (Qualtrics International Inc) [65]. Refer to Table 1 for a summary of the outcomes and instruments used in this study and Table 2 for the study timeline.

**Table 1 table1:** Summary of outcome measures and instruments.

Outcome measures		Instrument
**Primary outcome measures**		
	Background and demographic data	Demographic questionnaire MoCA^a^ GDS-15^b^ GAQ^c^
	Feasibility, usability, and accessibility of at-home VR^d^ exergaming	Self-reported physical (eg, motion sickness, vertigo, or nausea) or emotional (eg, fear or anxiety) discomfort Ad hoc usability and game user experience questionnaire Perceived enjoyment Exergaming session adherence rate Informal notes and reports Semistructured focus groups or interviews
	Feasibility of the study protocol	Consent and recruitment rate Attrition and retention rate Activity log Rate of missing data Semistructured focus groups or interviews
**Secondary outcome measures**		
	Physical activity level	PASE^e^ RPE^f^
	Executive function	Modified flanker task OTMT^g^ (part A and B) VF^h^ (animal naming)
	Multisensory integration and temporal perception	RT^i^ task SJ^j^ task SIFI^k^ TOJ^l^ task
	Affect	PAAS^m^
	Exercise self-efficacy	Bandura exercise self-efficacy scale

^a^MoCA: Montreal Cognitive Assessment.

^b^GDS-15: Geriatric Depression Scale-15.

^c^GAQ: Get Active Questionnaire.

^d^VR: virtual reality.

^e^PASE: Physical Activity Scale for the Elderly.

^f^RPE: rate of perceived exertion.

^g^OTMT: Oral Trail Making Test.

^h^VF: verbal fluency.

^i^RT: response time.

^j^SJ: simultaneity judgment.

^k^SIFI: sound-induced flash illusion.

^l^TOJ: temporal-order judgment.

^m^PAAS: Physical Activity Affect Scale.

**Table 2 table2:** Summary of the study timeline.

Outcome measure and instrument		Time points																			
		Baseline	Week 1			Week 2			Week 3			Week 4			Week 5			Week 6			Follow-up
			Before	After	Before		After	Before		After	Before		After	Before		After	Before		After		
**Background and demographics**																					
	Demographic questionnaire	✓																			
	MoCA^a^	✓																			
	GDS-15^b^	✓																			
	GAQ^c^	✓																			
**Executive function**																					
	OTMT^d^ (A and B)	✓	✓	✓				✓		✓				✓		✓				✓	
	VF^e^	✓	✓	✓				✓		✓				✓		✓				✓	
	Modified flanker task	✓	✓	✓				✓		✓				✓		✓				✓	
**Multisensory** **i** **ntegration and temporal perception**																					
	SIFI^f^ task	✓			✓		✓				✓		✓				✓		✓	✓	
	SJ^g^ task	✓																		✓	
	TOJ^h^ task	✓																		✓	
	RT^i^ task	✓	✓	✓				✓		✓				✓		✓				✓	
**Physical activity, mood, and exercise self-efficacy**																					
	PAAS^j^	✓	✓	✓	✓		✓	✓		✓	✓		✓	✓		✓	✓		✓	✓	
	PASE^k^	✓																		✓	
	Exercise self-efficacy	✓					✓						✓						✓		
	RPE^l^			✓			✓			✓			✓			✓			✓		
	Perceived enjoyment			✓			✓			✓			✓			✓			✓		
Usability and game user experience questionnaire																				✓	

^a^MoCA: Montreal Cognitive Assessment.

^b^GDS-15: Geriatric Depression Scale-15.

^c^GAQ: Get Active Questionnaire.

^d^OTMT: Oral Trail Making Test (part A and B).

^e^VF: verbal fluency (animal naming).

^f^SIFI: sound-induced flash illusion.

^g^SJ: simultaneity judgment.

^h^TOJ: temporal-order judgment.

^i^RT: response time.

^j^PAAS: Physical Activity Affect Scale.

^k^PASE: Physical Activity Scale for the Elderly.

^l^RPE: rate of perceived exertion.

##### Feasibility of the Study Protocol and VR Exergaming

The rates of recruitment, attrition, retention, and missing data will be used to assess the feasibility of the study protocol. The feasibility, usability, and accessibility of *Seas The Day* will be assessed using quantitative and qualitative data. Quantitative data will be collected from (1) an ad hoc usability and game user experience questionnaire, (2) the participants’ adherence rate to the exergaming sessions, and (3) the participants’ perceived enjoyment. Qualitative data will be obtained from (1) self-reported physical (eg, motion sickness, vertigo, or nausea) or emotional (eg, fear or anxiety) discomfort (if any), (2) the participants’ informal notes and reports, and (3) semistructured focus groups or interviews.

The ad hoc usability and game user experience questionnaire is developed by the research team. Subscales of validated usability and acceptability models [66,67] are used in this questionnaire to explore users’ attitudes and intentions of using VR exergame systems (eg, perceived usefulness, perceived ease of use, perceived enjoyment, and intention to use in the future). The participants will be asked to rank each question from 1 to 5 based on how much they agree with each statement. The participants’ perceived enjoyment will be assessed using a paper-based, pictorial 5-point Likert scale ranging from *not enjoyable at all* to *extremely enjoyable*.

Semistructured focus groups or interviews (approximately 60 minutes) will be conducted to obtain in-depth information regarding each participant’s experience of the study procedures and measures. For the experimental group in particular, focus groups or interviews will be used to gain more insight into the participants’ perceived feasibility, acceptability, and usability of the VR exergaming system (eg, satisfaction, ease of use, engagement, safety, and motion sickness). Facilitators of and barriers to the adoption of and adherence to the VR exergaming system will also be explored in focus groups or interviews. For the control group, the focus groups or interviews will be used to gain insight regarding technology use and adoption and obtain feedback on the web-based tasks and assessments.

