Focus groups or interviews will be digitally recorded (via videoconferencing platforms) and transcribed verbatim. All qualitative data (ie, focus groups or interviews, self-reported physical or emotional discomfort, and the participants’ informal notes and reports) will be organized and coded using NVivo (version 12; QSR International) [86]. Inductive and deductive thematic analyses (informed by the feasibility, usability, and acceptability objectives of the study) will be performed after line-by-line coding to identify key topics and patterns of meaning across the data [87-89]. Open coding and axial coding will be conducted by multiple researchers independently to enhance the rigor of data analysis [89-91]. Researchers will use reflexive memos during the coding process to reflect on the emerging themes and patterns [87,92,93]. To create a robust codebook, researchers will regularly meet to resolve any coding challenges or discrepancies. The codebook will be refined by discussing the coding scheme (as different key topics emerge) and merging or deleting overlapping codes. After a consensus is reached, the codebook will include definitions and examples of each code, and the coding process will continue until data saturation (ie, no new data and no new themes are observed) [94,95]. Codes will then be categorized to detect overarching themes as well as subcategories to support themes [87].

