## Results

This study aims for an estimated adherence rate of ≥80%. To minimize potential attrition, all participants will be provided with a thorough remote one-on-one explanation of the anticipated participation burden (time commitment) at baseline. The participants will also be contacted regularly throughout the data collection process to maintain a good working relationship and answer any questions that they may have. The participants may choose to withdraw from the study at any time and for any reason. However, they will be asked if their collected data can be used by the research team for information and data analysis purposes.

We anticipate that most of the enrolled participants will adhere to the study and follow the protocol. However, potential challenges related to nausea and motion sickness when interacting with the VR technology may lead to some dropouts in the experimental group [105-108]. Challenges related to remote assessments as well as the length and complexity of the cognitive and multisensory integration tasks may also result in attrition [109-112].

In addition, we anticipate that most participants will learn how to navigate virtual environments and successfully perform the proposed physical activities within the different stages of our exergame [113,114]. This can potentially lead to high levels of perceived enjoyment and study adherence, as found in similar studies using immersive VR with the same duration and frequency [115]. However, it is also expected that some older adults might need more support than others to set up the VR system and adapt to the technology [113,114,116,117]. These supports might need to be individualized and tailored as the pilot progresses.

Both the experimental and control conditions have been reviewed and received ethics clearance through the University of Waterloo Research Ethics Committee (experimental condition ethics clearance in April 2021 and control condition ethics clearance in June 2021). The screening and recruitment process for the experimental group started in May 2021, and the data collection process will be completed by September 2021. As of August 16, 2021, 15 community-dwelling older adults have enrolled in the experimental group, of whom 2 (13%) have dropped out. The recruitment process and data collection for the control group will start in September 2021 and be completed by December 2021.

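### Discomfort from the headset is listed under the primary outcomes but is planned only as qualitative data, so no symptom rate with a defined denominator will come out of the pilot

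*Protocol article*

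**What the plan says.** In the protocol article, Table 1 lists "Self-reported physical (eg, motion sickness, vertigo, or nausea) or emotional (eg, fear or anxiety) discomfort" under the primary outcome measures, as the first instrument for feasibility, usability and accessibility of at-home VR exergaming.

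The section Feasibility of the Study Protocol and VR Exergaming divides the data for that outcome in two. On one side, "Quantitative data will be collected from (1) an ad hoc usability and game user experience questionnaire, (2) the participants’ adherence rate to the exergaming sessions", with perceived enjoyment as the third item. On the other, the qualitative data begin with "self-reported physical (eg, motion sickness, vertigo, or nausea) or emotional (eg, fear or anxiety) discomfort (if any"), followed by informal notes and by focus groups or interviews.

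The Feasibility Analysis section defines rates for recruitment, attrition and adherence. It defines none for discomfort. It groups "self-reported physical or emotional discomfort" with the interview material for coding and thematic analysis.

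The Overview under Outcomes and Measures says that "the experimental group will complete the RPE [64] and perceived enjoyment scales upon completion of each exergaming session". It mentions no symptom item there, and Table 2 has no row for discomfort.

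Motion sickness does appear elsewhere. The end-of-study focus groups or interviews explore "usability of the VR exergaming system (eg, satisfaction, ease of use, engagement, safety, and motion sickness"), and the Results section says that "potential challenges related to nausea and motion sickness when interacting with the VR technology may lead to some dropouts" in the experimental group.

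**The concern.** Enjoyment and exertion are rated on fixed scales after sessions, so each has a numerator, a denominator and a date. Headset discomfort also sits under the primary outcomes, and the authors foresee it as a risk: people prone to motion sickness are excluded, and the Results and Discussion sections both anticipate the problem. Yet the described plan gives it neither a structured measure during play nor a quantitative summary.

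The stated purpose of the pilot is to inform a larger trial. That trial will need to know how many users have symptoms, how severe they are, and whether they fade or persist over sessions. Themes from coded text explain experience but do not answer those questions. A small number of remarks could also be read as good tolerability when it only reflects who happened to speak.

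**Working it through.** **1. The plan's own related figure.** The Results section reports 2 dropouts among 15 enrolled in the experimental group by August 16, 2021. 2/15 = 13.3%, which agrees with the stated 13%. The exact 95% confidence interval is 1.7% to 40.5%. The article does not give the reasons for the two dropouts.

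**2. What is and is not measured.**

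| Item | Class of data | Fixed scale after play | Rate or score planned |
|---|---|---|---|
| Enjoyment | quantitative | yes | yes |
| RPE | secondary outcome | yes | yes |
| Adherence | quantitative | not applicable | yes |
| Discomfort | qualitative | none described | none described |

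The Physical Activity Affect Scale (PAAS) is scheduled before and after play in every week. Its 12 items cover positive affect, negative affect, exhaustion and tranquility. None is nausea, vertigo or dizziness.

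**3. Effect of incomplete reporting (illustration).** Let p be the true proportion of participants with symptoms and s the fraction of those whose symptoms are recorded. Both are assumptions; the documents give neither. With n = 12 (the minimum target per group), the expected observed proportion is p × s, and the chance of no report is (1 − p × s)^12.

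| p | s = 1 | s = 0.5 | s = 0.25 |
|---|---|---|---|
| 0.10 | 28.2% | 54.0% | 73.8% |
| 0.20 | 6.9% | 28.2% | 54.0% |
| 0.30 | 1.4% | 14.2% | 39.2% |

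Example: p = 0.20 and s = 0.5 give 0.90^12 = 28.2%.

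**4. Effect of missing dropouts (illustration).** Suppose both dropouts left because of sickness and were not interviewed, and 1 of the 13 others was affected. The interviews would show 1/13 = 7.7%, against (1 + 2)/15 = 20.0% in truth. If the dropouts' reports are captured, this bias disappears.

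**5. What a structured item would give.** Three sessions a week for 6 weeks is 18 sessions. Twelve participants would give 12 × 18 = 216 scheduled answers, and 15 would give 15 × 18 = 270. If the sheet were completed only once a week, as the single after-play column per week in Table 2 could be read, 12 participants would give 12 × 6 = 72. Per-participant precision stays low: 0 of 12 has an exact 95% interval of 0% to 26.5% (upper limit 1 − 0.025^(1/12)), and 3 of 12 has 5.5% to 57.2%.

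**The case against.** The strongest reply is that a mixed-methods pilot may choose qualitative capture, and that the article does not say how discomfort is elicited. Self-report need not be unprompted. The qualifier about whether any discomfort occurs proves little, since the article uses the same phrase for baseline depressive symptoms, which are measured with a fixed 15-question scale. The missing row in Table 2 is weak evidence too, because interviews, informal notes and the activity log have no row either. The log, the usability questionnaire items, the operating procedures and the interview guide are not shown and could hold symptom questions. All of this stands. It does not alter the stated classification as qualitative data or the stated thematic analysis.

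There are also other points at which discomfort could surface. Participants think aloud with a team member at the introductory session, are contacted every 2 weeks, and may choose a one-to-one interview. The PAAS overlaps with general emotional and physical discomfort. These make it less likely that marked symptoms go unnoticed, but none is described as a symptom enquiry with a recorded answer for every participant.

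A reader might infer more than the text supports:

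- *That symptoms are recorded only if volunteered, with no scheduled question at all.* The article does not say reports are unprompted, and the scheduled end-of-study interview names motion sickness.
- *That no rate could be obtained.* Participants with coded discomfort could be counted. Such a count is not planned, and who was asked would be unclear.
- *That the true rate will certainly be understated.* No reporting fraction is given. Under-reporting is likely, not established.
- *That motion sickness is the expected cause of dropout.* It is one possible cause; remote assessment and the length and complexity of the tasks are named as well.

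Finally, excluding people prone to motion sickness may lower the true rate, so the higher values of p in the illustration may not apply.

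**Conclusion.** The point holds as a limited one. An outcome listed under the primary measures is explicitly classed as qualitative and analysed only by theme, with no structured VR-symptom item described for the intervention weeks and no discomfort rate planned. The pilot as described therefore gives no incidence, severity or timing over a defined denominator. Under-reporting is likely, the more so if people who drop out are not interviewed.

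The size depends on assumed values. At a true 20% with half of it recorded, a result of no reports among 12 has a 28% chance, against 7% with full reporting. At a true 30% the figures are 14% and 1%. Asking everyone would not make 12 participants precise, but it would make the proportion interpretable. This is an inexpensive improvement to a declared design choice, not an arithmetical error or an internal contradiction.

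**What to change.** Add brief fixed items (nausea, dizziness or vertigo, eye strain, anxiety; each none, mild, moderate or severe) alongside the paper RPE and enjoyment scales completed after sessions, and add a row to Table 2. In the Feasibility Analysis section, plan the number and percentage of participants, and of sessions, with any symptom and with a moderate or severe one. Use everyone who started a session as the base, with exact confidence intervals for the participant-level proportions; session-level percentages should allow for repeated sessions within a person or be left descriptive. Keep the thematic coding to explain the counts.

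Fifteen participants had enrolled by August 2021, with collection in that group due to end in September. For those under way or finished, ask the same items at the remaining 2-weekly check-ins and at the end-of-study contact, and seek answers from dropouts where they agree. Report prompted answers and earlier unstructured reports separately.

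The cost is under a minute per session and a minor ethics amendment. Prompting will raise the reported symptom rate, and ascertainment will be mixed among those already enrolled.
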